#### Randomization: Arm 2—Participants Allocated to Moodzone

Participants will be directed to the Moodzone area of the NHS Choices website, a free to access website providing information on mental health conditions and locally available resources. Participants will be able to access all of the available material on mental health, including depression and anxiety. The site contains reading material and suggestions about maintaining mental health and provides measures of depression and anxiety for visitors to use.

All participants will be asked about whether they have received or used any additional mental health resources during their time in the study. NHS Moodzone access is used as the control digital resource so that all the participants are offered some help for their problems with depression or anxiety, but the control group do not access moderated, anonymized peer social support.

### Outcome Measures

Once consented, participants will be asked to complete self-rated questionnaires to measure well-being, depression, anxiety, work and social adjustment, QOL (for economic analysis), receipt of services (for economic analysis), social support, and personality dysfunction (see Table 1). These will be completed online (through the study website) in approximately 20 to 30 min, with the primary outcome data collected first. All data will be stored on the website and downloaded and anonymized by the clinical trials manager.

#### Primary Outcome Measure

Change in self-rated well-being at from baseline to 3 and 6 weeks after baseline using the 14-item Warwick-Edinburgh Mental Well-Being Scale (WEMWBS)

#### Secondary Outcomes Measures

Maintenance of well-being 12 and 26 weeks using the WEMWBSGAD-7 scale—completed as part of eligibility at baseline and then at 3, 6, 12, and 26 weeks as a brief measure of the severity of 7 symptoms of anxietyPHQ-9—completed as part of eligibility at baseline and then at 3, 6, 12, and 26 weeks as a measure of depression severity according to the *Diagnostic Statistical Manual, 4th edition* criteria [27]12-item Medical Outcomes Study Short Form health survey version 2.0 (SF-12v2) [28]—a short and practical measure of health-related QOL derived from the longer SF36 that is obtained during interviewSocial support is measured using the 8-item Medical Outcomes Study Social Support Survey (MOS-SS) [29], and it is completed at baselineSocial function on the 8-item Work and Social Adjustment Scale (WSAS) [30]—a simple measure of impact on function, which is attributable to a particular cause such as depression or anxiety. It is completed at baseline and then at 3, 6, 12, and 26 weeks

Mediators of the effectiveness of BWW compared with Moodzone on mental well-being might be the emotional and informational support subscales of the MOS-SS [29]. Data collected by BWW suggest that perceived social support might be an important mediator of outcome, particularly in people experiencing life events and loneliness.

Moderators of outcome at baseline might be the presence of life events in the previous 6 months, measured by the 12-item Brugha Inventory of Life Events [31], and the presence of anxiety alone at baseline. Personality dysfunction will be measured at baseline using the 8-item Standardised Assessment of Personality-Abbreviated Scale (SAPAS) [32]. There may be an interaction between the presence of life events at baseline and greater perceived emotional support from BWW at 3 months and on mental well-being at 6 months, whereas higher scores on the SAPAS may predict dropout and little difference between the treatment arms on mental well-being at 6 weeks.

**Table 1 table1:** Timing and delivery of outcome measures.

Measure	Baseline	3 weeks	6 weeks	12 weeks	26 weeks
WEMWBS^a^	Website	Website	Website	Website	Website
PHQ-9^b^	Website	Website	Website	Website	Website
GAD-7^c^	Website	Website	Website	Website	Website
WSAS^d^	Website	Website	Website	Website	Website
MOS-SS^e^	Website	X^f^	X	X	X
SAPAS^g^	Website	X	X	X	X
Brugha Life^h^	Website	X	X	X	X
SF12-v2^i^	Website	X	X	X	Interview
CSRI^j^	Website	X	X	X	Interview

^a^WEMWBS: Warwick-Edinburgh Mental Well-Being Scale.

^b^PHQ-9: 9-item Personal Health Questionnaire.

^c^GAD-7: 7-item Generalized Anxiety Disorder Scale.

^d^WSAS: Work and Social Adjustment Scale.

^e^MOS-SS: 8-item Medical Outcomes Study Social Support Survey.

^f^X: Measures are not collected at this time point.

^g^SAPAS: Standardised Assessment of Personality-Abbreviated Scale.

^h^Brugha Life: 12-item Brugha Inventory of Life Events.

^i^SF-12v2: Medical Outcomes Study Short Form health survey version 2.0.

^j^CSRI: Client Service Receipt Inventory.

To explore the reach, adoption, and implementation arms of the RE-AIM framework, a number of process measures will be recorded as the study progresses:

Live log of services, individuals, groups, and charities that are approached to engage with the study. The networks that surround these and how this may spread will be recorded and used to determine reach and adoption. A network of practice comprising all health care stakeholders will be established to explore implementation pathways.Reach will be further explored using Internet analytic software or to derive anonymous data around hit and bounce rates, pages visited, length of visit, type of geography, and simple demographics to the study website can be recorded, downloaded, and analyzedImplementation will be explored when highlighting the barriers and drivers to reach, effectiveness, and adoption assessed through qualitative work with the services, groups, and individuals engaged through recruitment, as well as an economic evaluation of its costs and cost-effectiveness from personal, social, and health care perspectives. In particular, we will explore how participants utilize BWW in relation to the literature on similar websites offering peer support and information for physical illness and literature on social and organizational aspects of depression and anxiety care.Working with the local Academic Health Science Network to record the take-up by organizations and implementation (number, percentage, and representativeness in East Midlands) of BWW across the East Midlands after the trial has been completed should it prove to be clinically and cost effective.

In terms of socioeconomic inequalities, we will record the following provided such detailed recording of information does not deter participation: postcode, age, gender, ethnicity marital status, highest level of education, and employment.

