### Expected Duration of Participant Participation

Participation in the study will be for 6 months (see Figure 1 for participant journey through the study). Participants will receive electronic follow-up invitations at 3, 6, 12, and 26 weeks after randomization to be completed on the website. Participants may also be asked to take part in a short interview by phone or face-to-face to talk about their experiences of services and/or the study no later than 3 months from the ending of their participation.

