### Sample Size and Justification

Given that the focus of BWW is on improving mental well-being rather than specifically depression or anxiety, a clinically important difference on the WEWBS was selected as the primary outcome. Data from BWW online support groups show clinically important differences in depression by 6 weeks, so the primary outcome will be a change in the WEWBS from baseline to 3 and 6 weeks. The minimal clinically important difference (MCID) for adults on the 14-item WEWBS with mild to moderate depression and anxiety is 3 points and WEWBS scores are normally distributed [24]. On the basis of data from a Web-based CBT intervention versus information from an RCT in a similar participant group with a similar design [33], and inflating the variance (to allow for contamination) at 6 weeks by almost 50%, we estimate the sample size required to detect a 3-point MCID between the BWW and Moodzone groups at 6 weeks to be 676 in total or 338 per treatment group using the analysis of covariance method with 90% power to show a difference at two-sided 5% significance level assuming zero correlation between pre- and posttreatment outcomes. In the previous study, the intervention and control groups were 42.20 (standard deviation [SD] 9.83) and 42.32 (SD 9.64), respectively, and by 6 weeks they were 44.46 (SD 8.1) and 41.92 (SD 9.18). In the power calculation, we have assumed that at baseline, each intervention group will have a mean baseline score of 42.20 (SD 9.83) and that this will increase to 44.46 (SD 12.0) in BWW and fall slightly to 41.46 (SD 12.0) in the Moodzone control group at 6 weeks. There are no data currently available using the WEWBS with BWW, but BWW online support groups show a drop in PHQ-9 score from 13.9 (SD 7.1) to 8.6 (SD 6.5) at 6 weeks—a change that is equal to an MCID of 5.0 points suggesting that BWW can produce clinically important differences in outcome.

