### Statistical Analysis

Analysis of the primary and secondary outcome measure data will be carried out by the trial statistician, who will remain blind to arm allocation, using STATA 14.

In a RE-AIM study, all outcomes are considered to address important facets of a public health intervention. Therefore, we will examine reach (the percentage and representativeness) of participants entering the trial. Exploratory analysis will summarize outcome variables and participant background variables by treatment arms across follow-up time with mean (SD) for normally distributed data, median (interquartile range) for skewed variables, and frequency (percentage) for observed level of categorical variables. The analysis to examine the treatment effect will be performed on an intention-to-treat basis. As the primary outcome WEWBS score will be repeatedly measured at baseline, 3 weeks, and 6 weeks, multilevel modeling will be performed to quantify the treatment effect with participant as a level 2 unit and baseline measurement as a covariate using Stata 14. Missing values will be imputed using a multiple imputation approach under a missing at random assumption. Path analysis will be used to explore changes in perceived emotional social support and empowerment at 3 weeks as potential mediators for treatment effects on mental well-being at 6 weeks, alongside life events, loneliness, having a partner, gender, age, anxiety without depression, and personality dysfunction at baseline as possible moderators for treatment effect. Such information will provide important information to refine both the targeting and content of BWW to optimize its reach and effectiveness.

A detailed statistical analysis plan setting out full details of the proposed analyses will be finalized before the trial database is locked for final analysis. Stata 14 will be used to perform exploratory data analysis and multilevel modeling, Mplus software (Muthen & Muthen, USA) will be used to perform path analysis [36].

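### The exploratory mechanism analysis is stated inconsistently: the outcomes section and the analysis section differ on mediators and time points, and neither mediation version can be run on the measures scheduled

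*Protocol article*

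**What the plan says.** The Protocol article describes the mechanism question in two places.

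Secondary Outcomes Measures makes two separate statements. The first is about mediators and carries no time point: "Mediators of the effectiveness of BWW compared with Moodzone on mental well-being might be the emotional and informational support subscales of the MOS-SS". The second concerns life events and emotional support only. It opens "There may be an interaction between the presence of life events at baseline" and continues with "greater perceived emotional support from BWW at 3 months and on mental well-being at 6 months".

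Statistical Analysis says that path analysis will explore "changes in perceived emotional social support and empowerment at 3 weeks as potential mediators for treatment effects on mental well-being at 6 weeks". Life events, loneliness, anxiety without depression, personality dysfunction and some demographic variables are listed there as possible moderators. Informational support is not mentioned.

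On data collection, the bullet on social support in Secondary Outcomes Measures places the MOS-SS at baseline. Table 1 agrees: the MOS-SS row has an X at 3, 6, 12 and 26 weeks, and the footnote defines X as "Measures are not collected at this time point". Life events are also collected at baseline only. WEMWBS is collected at baseline and at all four follow-ups. Table 1 lists no instrument named for empowerment.

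**The concern.** Exploring moderators and mediators is a stated aim under Objectives and a claimed advantage under Strengths. Statistical Analysis says the results will help to refine whom BWW is aimed at and what it contains. A mechanism analysis used in that way should test the mechanism that the document proposes.

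As written, the life-events hypothesis concerns support at 3 months and well-being at 6 months, while the path analysis stops at 6 weeks. One section names informational support as a mediator and the other replaces it with empowerment. The emotional–informational distinction matters in this trial because the comparator is itself an information site, so the two kinds of support bear on what BWW adds to it.

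The measurement schedule makes the problem worse. A mediator must be observed after randomization. With the MOS-SS taken once, at baseline, no change in support can be calculated at either time point.

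**Working it through.** **Step 1. The two sections side by side**

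| Element | Secondary Outcomes Measures | Statistical Analysis |
|---|---|---|
| Mediators | Emotional and informational support (no time point) | Emotional support and empowerment |
| Time of support | 3 months (life-events sentence, emotional support only) | 3 weeks |
| Time of well-being | 6 months (life-events sentence) | 6 weeks |
| Role of life events | Interacts with perceived emotional support | Possible moderator of the treatment effect |

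**Step 2. Is the months version a real schedule?** Expected Duration of Participant Participation says "Participants will receive electronic follow-up invitations at 3, 6, 12, and 26 weeks after randomization". Taking 30.4 days to a month, 3 months is 3 × 30.4 / 7 = 13.0 weeks and 6 months is 6 × 30.4 / 7 = 26.1 weeks. These correspond to the 12- and 26-week follow-ups. Objectives also frames effectiveness over 3 months and maintenance over 6 months. The months version is therefore a workable alternative as well as a possible typing slip. The outcome times differ by 26 − 6 = 20 weeks.

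**Step 3. What can be run on the scheduled data (Table 1)?**

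- Change in emotional or informational support at 3 weeks: no, the MOS-SS is not repeated.
- Emotional support at 3 months: no, for the same reason.
- Change in empowerment at 3 weeks: no measure named for it is listed.
- Life events by arm on WEMWBS at 6 or 26 weeks: yes, both variables are scheduled. This model has no support term, so it tests only the moderation part of the hypothesis.

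**Step 4. The plan's own figure, as background for the SD.** Sample Size and Justification uses a 3-point difference, SD 12.0 in each arm, zero pre-post correlation and "90% power to show a difference at two-sided 5% significance level". The normal formula gives n per arm = 2 × (1.960 + 1.282)² × 12² / 3² ≈ 336.2, rounded up to 337. The t-based version gives 338, as stated. Power at 338 per arm is 0.901. With 50% loss, 676 / 0.5 = 1352, as stated. The sample size reproduces and neither supports nor weakens this point.

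**Step 5. Precision of the one feasible interaction test.** Assume a moderator present in 50% of participants, so four equal cells of N/4. The standard error of the interaction is 12 × √(4 / (N/4)) = 48 / √N, and the difference detectable at 80% power is (1.960 + 0.842) × SE.

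| N analysed | Basis | SE (points) | Detectable (points) |
|---|---|---|---|
| 676 | Plan's completers at 6 weeks | 1.85 | 5.2 |
| 473 | Assumed, 70% of 676, at 26 weeks | 2.21 | 6.2 |
| 338 | Assumed, 50% of 676, at 26 weeks | 2.61 | 7.3 |

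The 50% prevalence and the 26-week numbers are assumptions; the document gives neither. All three detectable interactions exceed the 3-point MCID, so the test is imprecise at either horizon.

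**The case against.** The strongest reply is that this is exploratory text. The outcomes section says what might or may be the case, and the analysis section speaks of exploring potential mediators and possible moderators. A confirmatory standard does not apply, and the final model is commonly left to a SAP. The life-events sentence goes on to give 6 weeks for its personality hypothesis, so months could be a slip for weeks, or the sentence could be a separate longer-term conjecture. The primary analysis is untouched.

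Most of this stands and sets the severity. It does not remove the point. Two sections of one document state different mediators and different times, which is more than detail left to a later plan, and a slip would still need correcting.

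A reader might be tempted by three stronger readings that the documents do not support:

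- *That the outcomes section defines mediation through both subscales from 3 to 6 months.* It does not. The sentence naming both subscales has no time point, and the sentence with the months names emotional support only.
- *That the horizon could be picked once results are known.* Statistical Analysis fixes one horizon for the path analysis and commits to a detailed SAP before database lock.
- *That omitting informational support inflates the emotional path by a known amount.* With equal mediator-to-outcome paths and equal variances, the ratio of the emotional coefficient without and with the second subscale is 1 + r, where r is their residual correlation. Any figure therefore restates an assumed r, and the document gives no path or correlation.

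**Conclusion.** The inconsistency holds and is minor. The planned path analysis differs from the stated hypothesis in horizon (3 and 6 weeks against 3 and 6 months), and its mediator list differs from the one in the outcomes section (empowerment in, informational support out). The baseline-only MOS-SS means that neither mediation version can be run as scheduled, so aligning the wording alone would not repair the analysis. These conclusions rest on the text and Table 1 and need no assumption. Only the precision of a 26-week interaction test rests on assumed retention and prevalence. The primary outcome, the sample size and the main treatment comparison are not affected.

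**What to change.** Before the SAP is finalized:

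1. State one mediator list in both sections: emotional and informational support, with empowerment only if it is measured.
2. State one horizon in both sections, and amend Table 1 so that the mediators are collected at the mediator time point. If that cannot be done, withdraw the mediation analysis.
3. Either correct the months in Secondary Outcomes Measures to weeks, or keep the 6-month hypothesis and pre-specify one exploratory life-events-by-arm interaction on 26-week WEMWBS. Label that test as addressing only the moderation part, and as imprecise on the assumptions shown in the working.

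The cost is wording in two sections, a slightly larger exploratory model, at most one extra exploratory test and, if the MOS-SS is repeated, eight more online items at that follow-up.

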### Sample Size and Justification

Given that the focus of BWW is on improving mental well-being rather than specifically depression or anxiety, a clinically important difference on the WEWBS was selected as the primary outcome. Data from BWW online support groups show clinically important differences in depression by 6 weeks, so the primary outcome will be a change in the WEWBS from baseline to 3 and 6 weeks. The minimal clinically important difference (MCID) for adults on the 14-item WEWBS with mild to moderate depression and anxiety is 3 points and WEWBS scores are normally distributed [24]. On the basis of data from a Web-based CBT intervention versus information from an RCT in a similar participant group with a similar design [33], and inflating the variance (to allow for contamination) at 6 weeks by almost 50%, we estimate the sample size required to detect a 3-point MCID between the BWW and Moodzone groups at 6 weeks to be 676 in total or 338 per treatment group using the analysis of covariance method with 90% power to show a difference at two-sided 5% significance level assuming zero correlation between pre- and posttreatment outcomes. In the previous study, the intervention and control groups were 42.20 (standard deviation [SD] 9.83) and 42.32 (SD 9.64), respectively, and by 6 weeks they were 44.46 (SD 8.1) and 41.92 (SD 9.18). In the power calculation, we have assumed that at baseline, each intervention group will have a mean baseline score of 42.20 (SD 9.83) and that this will increase to 44.46 (SD 12.0) in BWW and fall slightly to 41.46 (SD 12.0) in the Moodzone control group at 6 weeks. There are no data currently available using the WEWBS with BWW, but BWW online support groups show a drop in PHQ-9 score from 13.9 (SD 7.1) to 8.6 (SD 6.5) at 6 weeks—a change that is equal to an MCID of 5.0 points suggesting that BWW can produce clinically important differences in outcome.

The analysis will use multilevel modeling because of repeated measures in the same individuals. People directly participate in the study so there is no other form of clustering operating in this study. Our power calculation performed has already taken into consideration clustering because of repeated measures. Assuming a 50% loss to follow-up, a total of 1352 participants are required for the RCT [33,34] but typically BWW would be expected to enroll 2200 people in a county the size of Nottinghamshire if the uptake of BWW was consistent with the general pattern seen in similar parts of the country. Furthermore, in a study with a similar design [33], 3070 (63.52%, 3070/4833) participants who were enrolled into the study completed eligibility criteria on a website and were invited to take part. Taking a conservative approach, we would recruit approximately 1400 participants out of 2200 people meeting eligibility criteria and enrolling onto the study site. This would be sufficient to recruit an adequate sample size. Stata 14 (StataCorp LLC, USA) was used to perform power analysis [35].

### Randomization and Monitoring

The treatment to which a participant is assigned will be determined by a computer-generated pseudorandom code using random permuted blocks of varying size by a randomization system embedded within the website. No stratification or minimization is required. The outcome will be single-blind with the clinical trials manager and research associates responsible for the collection, cleaning, and analysis of the data remaining blind to arm allocation until data collection has been completed. Cases of unblinding will be recorded electronically but will not be excluded. Unblinding will only be necessary upon completion of data collection.

Overall, trial monitoring and oversight will be carried out by the CLAHRC-EM Scientific Committee who will act as the trial steering committee and data monitoring committee. The CLAHRC-EM scientific committee is composed of independent experts in statistics, epidemiology, medicine, and patient and public involvement. They will be sent quarterly reports on the status of the study and have the power to recommend or implement changes to the protocol if necessary. They are also able to stop the study if it is deemed unsafe or is failing to recruit after all avenues to recruitment have been exhausted.

There is no planned assessment of safety within the study design, and unless participants report any intercurrent illness or adverse events directly to the study team, it is unlikely that these can be recorded systematically.

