A further complication in the digital study is the issue of contamination. People with depression or anxiety might access BWW or Moodzone independently, although in the county of Nottinghamshire the opportunity to enroll in BWW is limited to access through the Armed Forces as new personal subscription has been suspended for the duration of recruitment and follow-up in the REBOOT study. Only one randomization is possible from each web browser within a 30 day period. Participants may be able to deceive the randomization process through access from a different computer or web browser or by clearing the cookie installed to prevent multiple attempts. Internet protocol (IP) address was not used as a marker to prevent multiple randomizations in case several people might be sharing the same computer. There may also be potential leakage with people who live outside Nottinghamshire using work postcodes that are within the county. Furthermore, there are potential problems with contamination through digital users utilizing alternative sources of digital support and information rather than the study treatment allocated to them. For instance people might join Facebook and offer support to each other even though it is not anonymized, and there is no profession moderation or support. If any of these occurred to a significant extent, it may be difficult to show real improvements in clinical and cost-effectiveness. To understand these potential sources of contamination, we are asking all participants about use of other sites.

The design of studies to evaluate the reach, adoption, clinical-effectiveness, and cost-effectiveness of direct to the public digital health interventions for mental health problems are important, given the reach, popularity, and low cost of such approaches in a world that is increasingly digitally connected even in the poorest countries of the world. However, we are in the early stages of understanding how to optimally design such studies.

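### Trials manager and research associates may be unblinded once data collection ends, with cleaning, SAP sign-off and database lock not required to come first

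*Protocol article*

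**What the plan says.** Three statements in the protocol article fix the blinding and its timing.

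- **Randomization and Monitoring** describes the clinical trials manager and research associates as "responsible for the collection, cleaning, and analysis of the data remaining blind to arm allocation until data collection has been completed". The same paragraph closes by repeating the trigger: "Unblinding will only be necessary upon completion of data collection".
- **Statistical Analysis** gives a different account of the analyst: "Analysis of the primary and secondary outcome measure data will be carried out by the trial statistician, who will remain blind to arm allocation". No end date is set for that blind.
- **Statistical Analysis** also says that the detailed analysis plan "will be finalized before the trial database is locked for final analysis". It does not link that date to unblinding.

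Two other sections show what the first group of staff handles. Outcome Measures says: "All data will be stored on the website and downloaded and anonymized by the clinical trials manager". Limitations concedes a problem that whoever cleans the data may meet: "Participants may be able to deceive the randomization process through access from a different computer or web browser".

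**The concern.** The end of data collection is an early point at which to release allocation to people who also clean the data. Some cleaning can remain after the last response arrives, and the database is locked only when it is done. If the same staff know the arms by then, choices about which records stay could be influenced by allocation, knowingly or not. The SAP may also still be open, so anyone unblinded who contributes to it would do so with allocation known.

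At stake is the composition of the dataset handed to the statistician. A blind statistician cannot undo selection that was made before the dataset was delivered.

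**Working it through.** There is no figure to reproduce: the point concerns the order of events and uses no alpha, power, SD or sample size. The check sets the statements side by side.

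1. **Who is covered by the early trigger.** Randomization and Monitoring names the clinical trials manager and the research associates. It lists collection, cleaning and analysis as three tasks but ties the blind to the first alone.
2. **When the SAP must be final.** The only deadline in Statistical Analysis is database lock. Lock cannot precede the end of collection, so the SAP may be finalized after the trigger has been met.
3. **What order the text allows.** Collection ends; the trials manager and research associates may be unblinded; cleaning is completed and the SAP may still be open; the database is locked; the final analysis follows. No sentence rules this out.
4. **Whether these staff have discretion that matters.** The trials manager downloads and anonymizes all the data. Limitations says that the block on repeat randomization works per web browser over 30 days, that it can be evaded by changing device or browser or by clearing the cookie, that IP address was not used for this purpose, and that people living outside the county may enter with a work postcode. Someone may have to decide what to do with such records. Those decisions concern which records count, so online self-rating of the scores does not remove them.
5. **Whether the open SAP has anything to settle.** The abstract places the primary outcome at 6 weeks. Primary Outcome Measure and the sample size section refer to change from baseline to 3 and 6 weeks, and Statistical Analysis describes a repeated-measures model over baseline, 3 and 6 weeks. The SAP would need to fix the primary contrast, so it matters whether it is signed before anyone who contributes to it is unblinded.
6. **Who is not covered.** Statistical Analysis keeps the trial statistician blind for the primary and secondary outcome analysis. That section assigns the analysis to the statistician, whereas Randomization and Monitoring counts analysis among the duties of the trials manager and research associates. The two sections therefore differ on who analyses and on how long the analyst stays blind.

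**The case against.** Four arguments can be made for the plan as it stands.

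- **The analyst is blind.** This stands, and it narrows the point. A reader might infer that the primary analysis itself will be done with allocation known. The document does not support that: the statistician who analyses the primary and secondary outcomes stays blind, with no time limit. Analysis decisions for those outcomes are exposed only if unblinded staff shape the SAP or the dataset.
- **The wording permits early unblinding but does not schedule it.** This also stands. The closing sentence of the paragraph can be read as ruling out anything earlier than the end of collection. In an automated website trial, much of the cleaning could run while data are still coming in. A reader should not conclude that cleaning will be done unblinded, only that nothing prevents it.
- **An article commonly leaves the order of cleaning, sign-off, lock and code release to fuller documents.** This is true of the detail, and its absence would not be a finding. But the article states the trigger, twice, and a SAP that may be finalized after that trigger cannot be assumed to correct it.
- **Discretion is limited.** Outcomes are self-rated online, analysis is by intention to treat with multiple imputation, and cases of unblinding are not excluded. This reduces the scope for bias in the scores and in the analysis set. It does not settle how duplicate or out-of-county records are handled.

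A reader might also try to size the problem as an inflated type I error, from a free choice between a 3-week and a 6-week contrast. That would measure something else. Such selection needs between-arm results and could be made with coded arms under a full blind, while learning the arm names does not by itself give anyone the choice of contrast.

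**Conclusion.** The point holds for the clinical trials manager and the research associates. The stated rule lets them be unblinded before cleaning is finished, the SAP is signed and the database is locked. Decisions about which records enter the dataset, and any contribution they make to the SAP, could then be made with allocation known. It does not extend to the trial statistician's analysis of the primary and secondary outcomes.

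The size of any bias cannot be quantified from the document. It depends on how many doubtful records arise, how much cleaning remains when collection ends, whether these staff are in fact unblinded then, and whether they contribute to the SAP. The document gives none of these. The conclusion rests on the wording of the rule alone. It is an inexpensive improvement to make, not evidence that the trial's result would be biased.

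**What to change.** In Randomization and Monitoring, replace the clause that ends the blind at the close of data collection with: *until data cleaning is complete, the SAP has been signed and the database has been locked*. Change the last sentence of that paragraph to give the same trigger. Apply both to the clinical trials manager and the research associates.

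Leave the trial statistician's blind in Statistical Analysis intact through the primary and secondary outcome analysis. Applying the lock trigger to the statistician as well would weaken the present text, because it would allow unblinding before that analysis is run.

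Reconcile the two sections on who analyses the data, so that one statement names the analyst and the duration of the blind.

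The cost is an edit to a few sentences, and the trials manager and research associates staying blind somewhat longer.
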